#### Exclusion criteria

Jaundice more than 3 monthsAST > 500 U/L or ALT > 300 U/L (not compatible with alcoholic hepatitis)Other concomitant causes of liver disease: viral hepatitis, autoimmune liver disease, metabolic liver disease, vascular liver diseaseHIV positiveCow milk allergy or severe lactose intoleranceActive gastrointestinal bleedingUncontrolled sepsis with multi-organ failureAcute kidney injury at time of randomization with creatinine > 2.5 mg/dLEvidence of acute pancreatitis or biliary obstructionSubjects who are pregnant or lactatingSignificant systemic cardio-pulmonary illnessPatients in shock, requiring the use of vasopressors or inotropic support in 12 h prior to randomizationTreatment for alcoholic hepatitis within 1 month of study entry with corticosteroid use > 1 week.Any patient who has received any investigational drug or device within 30 days of entering into the study.

All baseline assessments and eligibility criteria will be implemented before randomization.

## Experimental intervention: cow colostrum powder—a lyophilized (freeze-dried) colostrum (Annexure 1)

The herds of (Kankrej Cow breed) cows are kept under close supervision in good state of hygiene without exposure to antibiotics, pesticides, and anti-helminthics.

Only the milk of the first 12 h, when the nutrient concentration has its maximum value, is used. After this milk is milked from the mother cow, it is moved directly to the collection center in a stainless steel jar by authorized vendor of colostrum milk supplier in a refrigerated van with temperature control to maintain the quality of raw milk.

After weighing the milk and verification of weight/volume, it is subjected for quality check. Then filtration of milk is followed by continuous, high-temperature short-time (HTST) pasteurization at 71.7 °C for 15–20 s in a closed vessel. The pasteurized milk is stored in tray chiller freezer for 08 h at minus 30 °C. After completion of this process, the powder is packaged as per specifications. Testing is performed of freeze-dried bovine colostrum as per specification to ensure the consistency of powder.

Thus the steps of production of bovine colostrum are outlined below:

(1) Raw colostrum moved inward. (2) Quality check. (3) Storage in freezer. (4). Pasteurization process. (5). Storage in tray chiller freezer minus ( −) 30 °C (freeze drying), (6) Finished product quality check. (7) Finished products storage.

## Strategies to improve adherence to interventions

### Study intervention {11a}

#### Experimental arm (Group A): bovine colostrum

Bovine colostrum as a freeze-dried powder 20 g (dissolved in 100 ml of water) thrice a day will be given for 4 weeks.

### Side effects of bovine colostrum: {11b} allergy

#### Placebo comparator (Group B): pasteurized milk powder

Pasteurized milk powder 20 g (dissolved in 100 ml of water) will be given thrice a day for 4 weeks.

### Side effects of pasteurized milk powder: allergy

Both the bovine colostrum and the pasteurized milk powder will be of the same color, appearance, and taste.

### Criteria for discontinuing or modifying allocated interventions for a given trial participant {11b}

#### Occurrence of adverse effects of bovine colostrum (experimental arm) and pasteurized milk powder (placebo comparator): allergy

##### Permitted study drug adjustments

Study drug has to be taken in line with the treatment and dosage prescribed in the study. Any study drug adjustments can only be made by the Principal Investigator if as per his/her judgment, this will positively impact patient treatment. Further, any deviation from the laid out treatment in the study protocol will have to be documented giving justifications thereof.

### Strategies to improve adherence to intervention protocols, and any procedures for monitoring adherence (e.g., drug tablet return, laboratory tests) {11c}

All patients will be initially admitted in the hospital ICU / wards; hence, adherence to interventional protocol will be the responsibility of the Principal Investigator. After the patient is discharged from the hospital, the patients shall return for an outpatient visit. Participants will be contacted and reminded by telephone prior to the day of the outpatient visit at 7 days, 14 days, 21 days, 28 days, and then bimonthly for 2 months. On the outpatient visit, a history and physical examination of the patient will be conducted and details noted. The patients or their caregiver will return the empty sachets (and counted) and new batch of sachets will be given till the duration of the next outpatient visit. This process shall continue till the completion of 28 days of the study. Thereafter, the patients will be telephonically reminded to return for history, physical examination, and performance of laboratory tests till 90 days.

### Relevant concomitant care and interventions that are permitted or prohibited during the trial {11d}

Standard of care treatment will be given in both arms which are as follows:Oral + enteral nutrition (if oral intake is insufficient: protein 1.2–1.5 g/kg/day, energy (kcal) 35–40/day, B complex vitamins daily. [35]Nutrition education with dietitian including implementation of night-time snacks [36]Assess vitamin D levels in alcoholic hepatitis with underlying cirrhosis, as deficiency of vitamin D is highly prevalent. Supplement vitamin D orally with serum vitamin D levels < 20 ng/ml, to reach serum vitamin D (25(OH)D) > 30 ng/ml. In patients with alcoholic hepatitis with underlying cirrhosis and ascites, sodium restriction (recommended intake of sodium 80 mmol day = 2 g of sodium corresponding to 5 g of salt added daily to the diet according to disease) taking care to ease mildly sodium restriction to improve diet palatability [35].Antibiotics for sepsis; diuretics for ascites; lactulose / rifaximin / L ornithine L aspartate for hepatic encephalopathy; terlipressin, and albumin for type 1 hepatorenal syndrome; carvedilol for prophylaxis against variceal hemorrhage; terlipressin with endoscopic variceal ligation for variceal bleed, if indicated.Other concomitant medication

All medications (other than study drugs) and significant non-drug therapies (including physical therapy and blood transfusion) administered after the patient starts treatment with study drug must be listed on the Concomitant Medications/Significant Non-drug Therapies in the record file.

### Investigations (Annexure 2)

Each patient shall have an:

Abdominal ultrasonographyUpper gastrointestinal endoscopy would be done, if indicated.Liver biopsy: Percutaneous *or* transjugular liver biopsies may be obtained before start of therapy for diagnosis of alcoholic hepatitis. *Liver biopsy confirmation is needed in patients with confounding factors.*Laboratory tests: Hemogram, prothrombin time, blood glucose, liver function tests, blood urea, serum creatinine, and serum electrolytes will be done at baseline, and at 7 days, 14 days, 21 days, 28 days, and then bimonthly for 2 months or *earlier, if indicated.*Microbiologic tests: Blood cultures, urine culture, cultures of aspirates from endotracheal tubes in ventilated patients for aerobic and anaerobic bacteria, and fungi shall be done at admission. A diagnostic paracentesis will be done in all patients with ascites, at baseline, to diagnose spontaneous bacterial peritonitis. A repeat cell count (total and differential) shall be done on day 5 in patients diagnosed to have spontaneous bacterial peritonitis.A chest radiograph shall be done.Cytokine levels: Endotoxin, alphaTNF, and IL6&IL8 levels will be done at baseline and at end of treatment.Tests for etiologic evaluation

Etiology of hepatitis will be taken as *alcohol* if there is a history of significant alcohol intake (average consumption of more than three drinks (~40 g) per day for women and four drinks (~50–60 g) per day for men) for 6 months or more, with less than 60 days of abstinence before the onset of jaundice.

Each patient will be tested for:Hepatitis B surface antigen (HBsAg) and anti-hepatitis C (HCV) antibody using a third-generation commercial ELISA will be done for all patients.Wherever indicated, autoimmune hepatitis will be diagnosed when compatible clinical signs and symptoms, laboratory abnormalities (serum AST or ALT, and increased serum total IgG), serological (ANA, SMA, anti-LKM 1, or anti-LC1), and histological (interface hepatitis) findings are present.Wherever indicated, hemochromatosis will be diagnosed using serum iron, TIBC, transferrin saturation, and ferritin levels.

Wilson disease as suggested by liver disease seen in young patients (< 40 years) with

(A)Cirrhosis with chronic hepatitis, or(B)Acute hepatitis with liver failure (females–males being ratio 4:1) with severe jaundice, a slight elevation of the activity of transaminases, low alkaline phosphatase, and low hemoglobin concentrations (Coombs-negative hemolytic anemia) and acute renal failure.

Wilson’s disease diagnoses shall be confirmed only in these patients by the presence of Kayser-Fleischer rings, a low-serum caeruloplasmin concentration (less than 0.20 g/dl), and a raised 24-h urine copper excretion. In untreated symptomatic patients, “baseline” copper excretion greater than > 1.6 μmol/24 h (> 100 μg/24 h) is taken as diagnostic of Wilson’s disease. Hepatic copper concentration (on liver biopsy) ≥ 250 μg/g dry weight (considered diagnostic); < 50 μg/g almost always excludes diagnosis)

i.In addition, pregnancy test for females of childbearing potential will be done at baseline

### Outcomes {12}

#### Primary outcome measure

Survival at 3 months.

#### Secondary outcome measure

Survival at 1 monthChange in mDF/MELD at 1 monthChange in endotoxin levels at 1 monthChange in cytokines (alphaTNF, IL6&IL8 levels) at 1 monthNumber of episodes of sepsis (pneumonia, SBP, cellulitis, UTI) over 1 month

### Participant timeline {13}

Time schedule of enrolment, interventions (including any run-ins and washouts), assessments, and visits for participants. A schematic diagram is highly recommended (Fig. 2).

**Fig. 2 Fig2:**
[figure not shown]
Flow diagram

### Sample size determination {14}

In a recent Indian study, published in 2014 by Singh et al. [11] the mDf score was 77.4 (range 37–235), MELD score was 27.5 (range 19–41), and the survival rate was 22% at 90 days.

Hence, we calculated the sample size on the basis of the above study.

We consider a 20% increase in survival rate (80% power at 5% alpha) to be clinically meaningful and sufficient to change practice. To detect a 20% increase in survival (from 22 to 42%) in 3 months [the sample size was based on survival at a fixed time point (22% vs 42% at 3 months)], we require 79 patients in each group. Assuming 10% dropouts, the total sample size required for the study is 174.

### Recruitment strategies for achieving adequate participant enrolment to reach target sample size {15}

Regular Principal and Clinical Investigator meetings will be held to support trial recruitment and evaluate any recruitment challenges.

## Methods: assignment of interventions

### Allocation

#### Sequence generation {16a}

Enrolment of patients, assessing eligibility, recording of all baseline parameters, and obtaining informed consent will be carried out by Principal Investigator. Consecutive patients diagnosed to have SAH will be then registered by the site medical team onto the trial site via *Trans European Network for clinical trials services (TENALEA)*, a web-based registration and randomization system, and randomized into two groups (group A and B) to receive active drug or placebo 1:1. Non-eligible patients will be deemed screening failures.

#### Allocation concealment mechanism {16b}

Subsequently the TENALEA registration system will release the randomization code to non-study personnel in every center. Treatment allocation will be blinded to the patient or care giver or to the Principal Investigator by providing each patient with a unique number from the TENALEA registration system.

#### Implementation {16c}

The randomization code will be sent to non-study personnel in every center. These personnel will prepare closed envelopes with printed randomization numbers along with the corresponding code (A or B) for the treatment group.

Each center will have serially numbered identical sachets containing bovine colostrum or pasteurized bovine milk managed and administered to the patients by non-study personnel according to the random sequence. The drug and the placebo will be identical in color, taste, and appearance to ensure masking. The study drug will be administered by an oral route. The Principal Investigator and his team will have no information about the group allocation.

#### Blinding (masking) {17a}

The treatment arm will be concealed to patients, investigators (Clinicians), data collectors, outcome assessors, data analysts, and statistician. The randomization code will be revealed to the study statistician only after the completion of recruitment, data collection, and data analysis has been carried out.

#### Procedure for unblinding when necessary {17 b}

Unblinding may be permitted in the event of a medical emergency where breaking the blind is required to provide medical care to the subject.

Local Principal Investigators (PI) will have access to a mechanism that permits rapid unblinding should they feel this is necessary. *Local Standard Operating Procedures* describing the emergency unblinding procedure will be in place. The chief investigator recommends, but does not require, that the investigator contact him before breaking the blind. The rationale for unblinding must be clearly explained in source documentation and on the electronic case report form (eCRF), along with the date on which the treatment assignment information was obtained.

## Methods: data collection, management, and analysis

### Data collection methods {18a}

The Principal Investigator and his clinical trial team members will.Collect the primary and secondary outcome-related data: Baseline data (including USG abdomen and UGI endoscopy)Collect follow-up data, from participant visits. Duplicate measurements of all data will be collected.Obtain prior medications list and evaluate current medications.Collect blood for laboratory tests as per Annexure 2.

The principal means of data collection and storage from participant visits, permitted alteration to the intervention protocol, adherence to the interventions while admitted in the hospital, patient follow-up as outpatient visit, recording outpatient history and physical exam and laboratory data will be Electronic Data Capture (EDC) via the internet using the InForm database. Data is entered into the EDC system by site personnel. All source data recorded in the electronic case report form (eCRF) will be signed by the Investigator or his/her appropriate designee. All changes made following the electronic signing will have an electronic audit trail with a signature and date. Specific instructions and further details will be outlined in the eCRF manual.

### Data management {18 b}

The clinical trial team shall closely follow-up every patient at baseline (day 1), 4, 7, 21, 28, 45, 60, 75, and 90 days and remind him / her telephonically to attend all their scheduled outpatient visits till the end of follow-up at 3 months The team shall make a record of all outcome data collected for participants who discontinue or deviate from intervention protocols.

At each outpatient visit, medical history (together with a disease-specific history related to the patient’s diagnosis of severe alcoholic hepatitis) is taken and complete physical examination is performed. Primary and secondary outcome-related follow-up data, from participant visits, shall be accurately collected, and duplicate measurements of all data will be collected and recorded via the Electronic Data Capture (EDC) using the InForm database. All laboratory tests as mentioned in Annexure 2 will be performed and the laboratory test values recorded via the Electronic Data Capture (EDC) using the In Form database. The patient will be queried for adverse events, adherence to study medication, and intake of any concurrent medications and recorded in the In Form database.

### Data analysis {18c}

#### Statistical analysis

The Principal Investigator will assess the quality of the collected data by studying the InForm database collected by Electronic Data Capture (EDC). This includes Primary and Secondary outcome-related data including laboratory tests as per Annexure 2: baseline and follow-up data, from participant visits including record of all outcome data collected for participants who discontinue or deviate from intervention protocols.

### Data management {19}

The Principal Investigator will assess the quality of the collected data. All the data recorded in the electronic case report form (eCRF) will be signed by the Investigator or his/her appropriate designee. All changes made following the electronic signing will have an electronic audit trail with a signature and date. Specific instructions and further details will be outlined in the eCRF manual. The responsibility of coding, security, and storage of all data is with the *Trans European Network for clinical trials services (TENALEA).*

### Statistical analysis {20a}

#### Statistical methods

##### Statistical methods for primary and secondary outcomes {20a}

Subject population (S) for analysis

Common sensitivity analyses will be attempted to assess the robustness of the results to protocol deviations. For primary survival (efficacy) analysis, we will use intention to treat analysis, in such a way that all study subjects who are randomized, regardless of adherence to study medication, will be used in the analysis in the treatment arms to which they are originally assigned to at randomization (“as randomized”). Thus, the patient set used for the primary analysis according to the ITT principle is called “full analysis set”.

As a supplementary analysis, we will perform a per-protocol analysis using patients who will achieve at least 80% compliance (without any major protocol violations) with treatment arms. Significance will be assessed using a two-sided alpha level of 0.05.

#### Statistical methods

The baseline patients’ characteristics mentioned in Annexure 2 including comorbid-conditions will be compared between the two treatment groups to demonstrate the actual study group balance and to ensure whether a proper randomization is established or not. We will measure central tendency and variability with means and standard deviations or medians and interquartile range for continuous characteristics and frequencies with percentages for categorical characteristics.

For primary outcome “survival at 3 months,” we will first use an unadjusted log-rank test of the Kaplan–Meier survival estimates for the two treatment arms at a two-sided alpha level of 0.05 with survival censored at 3 months. Further, a Cox proportional hazards regression model (with survival censored at 3 months) will be used to estimate the hazards ratio (HR) with 95% confidence interval (CI) associated with treatment arm (A) compared to the reference treatment (B). Parameters which are observed as unbalanced between the groups will be adjusted in the above model. We will also add any potential time-dependent covariates to the model, such as AST and ALT levels at months 1, 2, and 3 to estimate their predictive value for mortality.

Similar unadjusted log-rank test of the Kaplan–Meier survival estimates, and Cox proportional hazards regression model analysis will be planned for secondary outcome survival at 1 month. Other secondary outcomes measures such as change in mDF levels/MELD score, endotoxin levels, and cytokines levels between baseline and 4-week assessment will be assessed for normal distribution by graphical (Q–Q Plot) interpretation and numerical method (Kolmogorov–Smirnov test). A paired *t*-test will be used for all those outcomes which will follow approximately normal distribution and a sign-rank test will be used for skewed parameters. Proportionality assumption will be assessed for the considered ordinal outcome number of episodes of sepsis (pneumonia, SBP, cellulitis, and UTI). Partial proportional odds ratio regression will be used to assess the effect of treatment on the number of episodes of sepsis (pneumonia, SBP, cellulitis, UTI) over 4 weeks. A proportional partial odds model will be used if the treatment group variable will not meet the proportional odds assumption and will have different effects on different severity levels of sepsis.

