#### Item 20b

##### Additional analysis

Subgroup analysis may be conducted based on the clinical age group criteria and grams of alcohol consumed criteria. The imbalanced baseline characteristics will not be included in the primary analysis; however, we will conduct additional exploratory analysis where such characteristics will be included to assess the robustness of the primary analysis.

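### Two incompatible rules govern covariate adjustment of the primary-outcome hazard ratio, and one of them lets observed imbalance choose the covariates

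*Protocol article*

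**What the plan says.** The primary outcome is "Survival at 3 months". For it, the Statistical methods section of the protocol article lays down a sequence. First, "we will first use an unadjusted log-rank test of the Kaplan–Meier survival estimates for the two treatment arms at a two-sided alpha level of 0.05"; follow-up is censored at 3 months. Next comes a Cox model, also censored at 3 months, that gives the HR and 95% CI for arm A against arm B. Of this Cox model the section says "Parameters which are observed as unbalanced between the groups will be adjusted in the above model". The following sentence adds time-dependent covariates to the model, with AST and ALT at months 1, 2 and 3 as examples.

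The Additional analysis section (Item 20b) then says "The imbalanced baseline characteristics will not be included in the primary analysis" and assigns models containing them to an additional exploratory analysis of robustness.

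The screening that feeds the rule is a comparison of the arms on the Annexure 2 baseline characteristics, whose stated purpose is "to demonstrate the actual study group balance and to ensure whether a proper randomization is established or not". The article gives no criterion for calling a characteristic unbalanced.

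**The concern.** The two sentences cannot both govern the Cox model under the primary outcome. One adjusts it for unbalanced parameters; the other keeps those parameters out of the primary analysis. Two analysts following the text in good faith could report different HRs and intervals as the treatment effect.

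The imbalance rule is also weak on its own terms:

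- Under proper randomisation, baseline differences are due to chance, so comparing the arms cannot establish that randomisation was proper.
- With no criterion stated, the covariates are settled only after the data are seen.
- What matters for precision is how strongly a covariate predicts death, not whether it differs between arms. The Background and rationale section itself treats MELD above 30 or mDF above 60 as marking a very poor outlook. Both scores are inclusion criteria, so every patient has them. Yet under the rule they enter the model only by accident.

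**Working it through.** **The plan's own figure.** "To detect a 20% increase in survival (from 22 to 42%) in 3 months", "we require 79 patients in each group". The implied HR is ln 0.42 / ln 0.22 = 0.573. Freedman's log-rank formula for two-sided 5% alpha and 80% power gives (1.960 + 0.842)² × (1.573 / 0.427)² = 106.5, so 107 events. The mean event probability is (0.78 + 0.58) / 2 = 0.68, and 107 / 0.68 = 157.4 patients, or 79 per arm. With 10% added, 79 × 1.1 = 86.9, so 87 per arm and 174 in total. The stated numbers reproduce and do not depend on this point.

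**How often the rule fires.** The number of characteristics screened and the threshold are assumed. With k independent comparisons at p < 0.05, the chance of at least one flag is 1 − 0.95^k:

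- k = 5: 23%
- k = 10: 40%
- k = 20: 64%

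**What the rule does to the HR and to power.** The simulation used 87 per arm, 3-month survival of 22% vs 42%, 10% of patients exposed to random early censoring, one severity score and nine irrelevant covariates, with 2,000 trials per scenario. The prognostic strength of severity is not in the documents, so a range is shown. The shift is the SD, among triggered trials, of the imbalance-adjusted minus the unadjusted log HR.

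| Assumed severity HR per SD | Power, unadjusted Cox | Power, severity always in | Power, imbalance rule | SD of log-HR shift | Significance differs, unadjusted vs rule |
|---|---|---|---|---|---|
| 1.0 | 82.7% | 82.6% | 81.8% | 0.044 | 2.0% |
| 1.5 | 86.1% | 89.5% | 85.7% | 0.069 | 2.4% |
| 2.0 | 87.9% | 96.3% | 88.3% | 0.097 | 2.1% |

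Power should be compared within a row. Always including severity gains 3.4 points (89.5 − 86.1) and 8.4 points (96.3 − 87.9) in the last two rows; the imbalance rule captures almost none of this. A separate run at 79 per arm (2,500 trials per scenario) points the same way: 83.9% to 86.3%, 83.2% to 90.7% and 83.9% to 94.2% for a log HR per SD of 0.3, 0.5 and 0.7.

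**Under no treatment effect**, for severity HR 1.0, 1.5 and 2.0 per SD:

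- Type I error of the imbalance rule: 4.75%, 4.4% and 3.4%.
- Type I error when either the unadjusted or the imbalance-adjusted result may be claimed: 4.9%, 5.0% and 4.65%.
- Disagreement on significance: 0.3%, 1.1% and 1.55%.
- SD of the log-HR shift: 0.038, 0.057 and 0.090.

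The Monte Carlo standard error at 5% is √(0.05 × 0.95 / 2000) = 0.5 points. Across all scenarios the shift runs from 0.038 to 0.097. Since exp(0.038) = 1.04 and exp(0.097) = 1.10, this is about 4–10% on the HR.

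**The case against.** The strongest reply is that the sections can be read together. The log-rank test comes first and is expressly unadjusted, the Cox model follows as estimation, and Additional analysis sets the hierarchy by making imbalance-driven models exploratory. An unadjusted primary analysis is valid under randomisation, covariate lists are often left to a statistical analysis plan, and the Blinding section keeps analysts and the statistician blind until the analysis is done.

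Most of this stands. The primary test is fixed and protected, and the lack of a named covariate list would not by itself be a finding. It does not settle the point, because Statistical methods directs the adjustment within the primary-outcome paragraph and does not label that model exploratory. A separate plan would still have to overrule one of two stated sentences. Blinding limits deliberate steering, but the covariates would still be chosen from the data.

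Three stronger readings are tempting and not supported:

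- A reader might infer that the choice between models inflates type I error or undermines the trial's p-value. The log-rank test is untouched, and even claiming the better of the two Cox results stays at 4.65–5.0%.
- A reader might infer that the trial gives up power on its primary test. The gain belongs to the Cox model under an assumed covariate strength; the log-rank test's power does not change.
- A reader might infer that baseline significance tests are planned. The section speaks of comparing the arms and lists summary statistics, but names no such test.

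**Conclusion.** The contradiction is real and is confined to estimation: the plan does not fix which HR and 95% CI accompany the log-rank test, and one of its two rules takes the covariates from the observed data. The typical consequence, when adjustment is triggered, is a change of about 4–10% in the HR, with the verdict on significance differing in about 2% of trials under the planned effect. Those sizes assume ten independent characteristics, a p < 0.05 threshold and a severity HR of 1.0 to 2.0 per SD. Interval coverage away from an HR of 1 was not examined.

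The unused severity information is a secondary matter. Its direction rests on the protocol's own account of MELD and mDF; its size, about 3 to 8 points of Cox-model power at an assumed HR of 1.5 to 2.0 per SD and none if severity is not prognostic, does not come from the documents.

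The primary test, alpha and sample size stand. This is a should-fix.

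**What to change.** 1. Keep the unadjusted log-rank test as the primary test.
2. Name in advance one Cox model for the reported HR and 95% CI: treatment, baseline severity (either MELD or mDF, chosen now and entered as continuous) and centre, fitted whatever the observed balance.
3. Delete from Statistical methods the sentence that adjusts for parameters found unbalanced. Keep imbalance-driven models exploratory, as Additional analysis already has it.
4. State that the time-dependent AST and ALT values are not in the model that gives the treatment HR. They are measured after randomisation, and while they remain in that model, deleting the imbalance sentence alone does not leave one clean HR.
5. Drop the claim that comparing baseline characteristics shows proper randomisation, and present the baseline table as description.

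The cost is text only. MELD, mDF and centre are already recorded for every patient, and no sample size or visit changes. The wording should be settled before the randomisation code is released and circulated through the route given in section {25}.

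### AST and ALT measured after randomisation are added to the Cox model that gives the treatment hazard ratio, so an HR from that model is not the intention-to-treat effect

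*Protocol article*

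**What the plan says.** The primary outcome is "Survival at 3 months". The Statistical methods section (item 20a) sets out four steps for it:

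1. The test: "we will first use an unadjusted log-rank test", two-sided at 0.05, with survival censored at 3 months.
2. The estimate: "Further, a Cox proportional hazards regression model (with survival censored at 3 months) will be used to estimate the hazards ratio (HR") with its 95% confidence interval (CI), arm A against arm B.
3. Baseline adjustment: "Parameters which are observed as unbalanced between the groups will be adjusted in the above model".
4. Later measurements: "We will also add any potential time-dependent covariates to the model, such as AST and ALT levels at months 1, 2, and 3". The sentence ends with the purpose, "to estimate their predictive value for mortality".

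A similar log-rank and Cox analysis is planned for survival at 1 month. Under Additional analysis (item 20b) the article states: "The imbalanced baseline characteristics will not be included in the primary analysis". That limit concerns baseline characteristics and says nothing about values measured during follow-up.

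**The concern.** Only one Cox model is introduced, and its job is to estimate the treatment HR. Steps 3 and 4 both add to it, so on a plain reading the AST and ALT values enter the model from which the HR and CI are taken.

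A covariate measured after treatment has begun can be altered by the treatment. Conditioning on it removes whatever part of the effect passes through it. The coefficient for arm then describes colostrum at a given AST and ALT. It is no longer the total effect of being assigned to colostrum, which the intention-to-treat analysis is meant to give.

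The log-rank test supplies no effect size, so the Cox HR is the only effect estimate with a CI that this section names for the primary outcome. A reader would take it as the size of the benefit. The covariate list is also open: AST and ALT are examples, and any other time-dependent covariate may join them.

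**Working it through.** **Timing.** Treatment lasts 4 weeks from randomisation, so values at months 1, 2 and 3 all follow its start. Survival is censored at 3 months, so a value taken then has almost no follow-up left in which to predict a death.

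**Causal path.** The section on luminal and liver action of bovine colostrum says that the product prevents the death of hepatocytes. AST and ALT are markers of hepatocyte injury, so on the protocol's own account they may lie between treatment and survival. The article gives no figure for the effect of colostrum on AST or ALT, or for their effect on mortality.

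**Does the planned size depend on this?** No. The assumed survival is 22% against 42%.
- HR = ln(0.42)/ln(0.22) = 0.573.
- Freedman's log-rank formula: events = (1.96 + 0.842)² × [(1 + 0.573)/(1 − 0.573)]² = about 107.
- Mean death probability = (0.78 + 0.58)/2 = 0.68, and 107/0.68 = 157.4, so 158 patients, or 79 per group.
- 158 × 1.1 = 174.

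Both stated figures, 79 and 174, are reproduced without any covariate.

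**How many deaths precede the first listed value?** With constant hazards:
- Placebo: (1 − 0.22^(1/3))/0.78 = 0.396/0.78 = 51%.
- Colostrum: (1 − 0.42^(1/3))/0.58 = 0.251/0.58 = 43%.
- Both arms: (0.396 + 0.251)/(0.78 + 0.58) = 48%.

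For about half of the deaths no month-1 value exists, which limits the distortion.

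**Illustration, with assumed mediation.** Treatment lowers a standardised marker by δ SD from the start, and the marker carries a log-HR of γ per SD. The total log-HR given the marker's pre-treatment value is ln(0.573) = −0.557, and the direct part is −0.557 + γδ. Placebo survival is set to 22%. The Cox model uses the pre-treatment value until month 1 and the treated value afterwards.
- Case 1: δ = 0.5, γ = 0.6. Mediated share = 0.30/0.557 = 54%.
- Case 2: δ = 0.7, γ = 0.75. Mediated share = 0.525/0.557 = 94%.

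| | HR, treatment only | HR with marker | Wald power, treatment only | Wald power with marker |
|---|---|---|---|---|
| Case 1 | 0.61 | 0.64 to 0.65 | 72 to 77% | 60 to 68% |
| Case 2 | 0.64 | 0.71 to 0.72 | 63 to 69% | 40 to 43% |

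The ranges cover repeated runs, including 79 and 87 (half of 174) patients per arm. The largest fall, 69% to 42%, and the case 1 fall of 77% to 68% come from the run with HRs of 0.71 and 0.64.

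A second illustration let the marker vary over time and updated it at months 1 and 2 (one run of 6,000 patients per setting):
- Treatment effect on the marker of 0.5 SD: HR 0.62 to between 0.65 and 0.66.
- Effect of 1 SD: HR 0.63 to 0.71 (γ = 0.3) or 0.64 to 0.79 (γ = 0.7).
- No effect on the marker: HR 0.61 to 0.59 (γ = 0.3) or 0.60 to 0.53 (γ = 0.7). This is no pull towards 1. The small move away from 1 is what adjustment for a prognostic covariate does to a Cox HR.

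**The case against.** The strongest defence is the purpose clause. The aim of the addition is the predictive value of AST and ALT. It comes last in a sequence, after the test and the treatment HR, so it can be read as a prognostic extension fitted once the HR has been reported. That aim is legitimate and the fix keeps it. But the clause does not change which model receives the covariates, and nothing says that the extended model yields no treatment HR. This is not a detail left to an analysis plan: the article states the addition itself.

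The second defence is that the primary test is untouched. This stands in full. A reader might infer that a real survival benefit could be declared absent. The document does not support that, because significance for the primary outcome is first assessed by the unadjusted log-rank test. The power losses above belong only to the Wald test in the extended Cox model.

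Third, a reader might infer a far larger distortion, for instance an HR near 0.78 or 0.97 with Wald power of 25% or 5% in the two cases. Those values arise only if the treated marker is known throughout follow-up. The article names values from month 1 onwards, by which time about half of the deaths have occurred.

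Fourth, the item 20b restriction shows that the primary analysis is meant to be unadjusted. It covers baseline characteristics only, and it sits awkwardly with the baseline adjustment in item 20a, so it does not settle the point.

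**Conclusion.** The point holds for the Cox HR and its CI. A treatment HR from a model that contains AST and ALT measured after randomisation is not the intention-to-treat effect. It is pulled towards 1 only to the extent that colostrum acts through those markers. It would go too far to say that part of any treatment effect is lost.

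The size rests on assumptions that the document cannot supply: the share mediated, the strength of the marker, and use of the pre-treatment value until month 1. Under these the HR moves from about 0.61 to 0.64 with half of the log-HR mediated, and from about 0.64 to 0.71 with nearly all mediated. The log-rank p-value, the Kaplan–Meier curves and the sample size are unaffected.

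The same applies to survival at 1 month only if the similar Cox analysis there takes in such covariates. A month-1 value arrives at the censoring time of that analysis, so the exposure there would come from earlier values admitted by the open wording. Conditioning on a marker that shares causes with death may add a further bias, but nothing in the document gives its direction or size, and the point does not depend on it.

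**What to change.** Replace the sentence on time-dependent covariates with three statements:

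- The treatment HR and 95% CI, at 3 months and at 1 month, come from a Cox model with treatment and, if any, prespecified baseline covariates only.
- Serial AST and ALT, named in a closed list, are studied in a separate model labelled as prognostic (time-dependent or landmark), from which no treatment effect is reported.
- The month-3 value is not used as a predictor, because follow-up ends there.

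This is a short change of wording in the protocol or analysis plan. It needs no extra patients or data, leaves the primary test and the planned 174 as they are, and keeps the prognostic question.
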